Although the relationship between oral health during pregnancy and birth outcomes has garnered increasing attention, effective oral care strategies for the prevention of PTB and LBW remain underexplored. Most interventional studies have found that basic periodontal treatment, which consists of scaling to remove plaque and calculus above the gingival margin and root planing to remove calculus below the gingival margin, is insufficient to prevent PTB and LBW [29, 30]. However, recent systematic reviews and meta-analyses suggest that combining scaling and root planing (SRP) with routine oral care using mouthwash containing chlorhexidine gluconate (CHG) may reduce the risk of PTB and LBW by approximately half (PTB: RR = 0.56; LBW: RR = 0.47) [31]. Another review found that the same combination significantly reduced the risk of PTB (OR = 0.29) and the composite outcome of PTB and/or LBW (OR = 0.18) [32]. The most recent meta-analysis further supported the effectiveness of combining SRP with any mouthwash, reporting a pooled RR of 0.44 for PTB and 0.33 for LBW [33]. Despite these promising results, there remains a lack of well-designed randomized controlled trials (RCTs) to confirm the effectiveness of this combined approach [31–33].

Given the urgent need to establish effective oral health management strategies for pregnant women, integrating oral health care into the MNCH CoC represents a promising and potentially scalable approach. This study therefore aims to (1) assess whether the association between periodontal disease and adverse birth outcomes observed in previous research is also evident in our study population, and (2) evaluate the effectiveness of an integrated intervention, combining SRP and CHG mouthwash use, delivered through MNCH CoC, in preventing PTB and LBW. This RCT will also examine the intervention’s impact on maternal periodontal status and oral health-related quality of life (OHRQoL). Demonstrating the effectiveness of this intervention could provide critical evidence for incorporating oral health into broader MNCH strategies. We believe this study offers a unique and timely contribution to improving MNCH outcomes through an oral health approach.

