### Randomization and blinding

The trial includes three groups: group A (intervention) and groups B and C (control). All participants will first complete a face-to-face interview at the obstetrics and gynecology department following consent. They will then undergo a baseline dental checkup. Participants diagnosed with periodontal disease will be randomized to group A or B using blocked randomization via computer-generated sequence at each site. Those without periodontal disease will be assigned to group C.

Blinding will be maintained for the interviewers and data recorders, who will not be informed of group allocation. However, blinding will not be feasible for the dentists conducting dental checkups or for participants due to the nature of the intervention.

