#### Surveys

Face-to-face interviews at baseline will collect data on socio-demographic characteristics, obstetric history, oral care behaviors, OHRQoL, and lifestyle. An endline survey, conducted post-delivery before hospital discharge, will obtain data on oral health care behaviors, OHRQoL, and lifestyle.

A structured questionnaire was developed in English, translated into Bengali, and then back-translated into English. The accuracy of the translation and reliability of the contents were reviewed by two native Bengali speakers with expertise in MNCH and dentistry. A pre-test was conducted to identify any biases or ambiguities and to assess whether the questions are culturally appropriate.

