#### Antenatal records

Data on birth outcomes, including gestational age at delivery and birth weight, will be extracted from antenatal records. Additional information will also be collected, including maternal height, pre-pregnancy body mass index, blood glucose level, pregnancy complications, and the number of antenatal checkups attended.

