### Statistical analyses

The primary analysis will follow the intention-to-treat principle, whereby participants will be analyzed according to their assigned groups, regardless of adherence to CHG mouthwash use during pregnancy. Missing data will be handled using multiple imputation procedures available in the MI suite of Stata. To assess the robustness of the findings, sensitivity analyses will be conducted by comparing results from imputed and non-imputed datasets.

Data from the baseline and endline surveys, dental checkups, and antenatal records will be compared across groups to evaluate the effects of the intervention (SRP combined with CHG mouthwash use) on the primary (PTB) and secondary outcomes (LBW, periodontal disease, and OHRQoL). Initial analyses will include descriptive statistics for participants’ socio-demographic and other basic characteristics, followed by bivariate analyses to examine differences in baseline variables between groups A and B, and between groups B and C.

To estimate the causal effect of the intervention on birth outcomes, comparisons will be made between groups A and B. To investigate whether previously reported associations between periodontal disease and adverse birth outcomes hold in our population, groups B and C will be compared.

For multivariable analyses, two types of regression models will be employed. (1) Multiple regression models will be used to evaluate outcomes measured only at endline. (2) Mixed-effect regression models will be applied for outcomes assessed at both baseline and endline, accounting for potential intra-individual serial correlations in the residual.

Specifically, to assess the effectiveness of the intervention on birth outcomes (PTB and LBW), a multiple regression model will be used, with intervention status (group A or B) as the main predictor, adjusting for potential covariates (socio-demographic characteristics, lifestyle, pregnancy-related characteristics, and pregnancy outcomes). For oral health outcomes (periodontal disease and OHRQoL), mixed-effects regression models will be used, including intervention status (group A or B), time point (baseline or endline), and their interaction terms, while adjusting for potential covariates.

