To evaluate the association between baseline periodontal disease and birth outcomes in groups B and C, a multiple regression model will be employed, with baseline periodontal status (group B or C) as the exposure, adjusting for potential confounders (socio-demographic characteristics and lifestyle at baseline). To assess change in periodontal status between baseline and endline in groups B and C, another multiple regression model will be used with similar covariate adjustments.

To evaluate the association of baseline periodontal diseases and OHRQoL in groups B and C, mixed-effect regression models will be fitted, including baseline periodontal status (group B or C), time point (baseline or endline), and their interaction term, adjusting for the possible confounding factors listed above.

Statistical significance will be set at a *p*-value of < 0.05. All statistical analyses will be conducted using IBM SPSS Statistics version 26.0 (IBM Corp, Armonk, NY, USA) or Stata version 16.0 (StataCorp LLC, College Station, TX, USA).

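### The adjustment set for the non-randomised B-versus-C comparison leaves out study site, pre-pregnancy BMI and maternal height, and is unclear on obstetric history

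*Protocol article*

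**What the plan says.** Women with periodontal disease are randomised to A or B, in blocks at each site. For the rest, Randomization and blinding states: "Those without periodontal disease will be assigned to group C". The Background gives the first aim as to "assess whether the association between periodontal disease and adverse birth outcomes observed in previous research is also evident in our study population", and Statistical analyses assigns that aim to the comparison of B with C.

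The same section names the covariates for each birth-outcome model:

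- **B versus C:** "adjusting for potential confounders (socio-demographic characteristics and lifestyle at baseline".
- **A versus B:** "adjusting for potential covariates (socio-demographic characteristics, lifestyle, pregnancy-related characteristics, and pregnancy outcomes".

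The two further B-versus-C analyses take over the shorter list. For change in periodontal status, "another multiple regression model will be used with similar covariate adjustments"; for OHRQoL, "adjusting for the possible confounding factors listed above".

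On what is collected, Antenatal records includes "maternal height, pre-pregnancy body mass index, blood glucose level, pregnancy complications" and the number of antenatal visits. Surveys says: "Face-to-face interviews at baseline will collect data on socio-demographic characteristics, obstetric history, oral care behaviors, OHRQoL, and lifestyle". The Socio-demographic data section, however, counts birth history among the socio-demographic items.

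**The concern.** Randomisation deals with baseline confounding between A and B. Nothing in the design does so between B and C, so that comparison is only as good as its adjustment set. The set is stated by category, and some variables fixed before the dental examination belong to neither category. A factor that predicts preterm birth, and whose frequency differs between women with and without periodontal disease, would then show up as part of the association attributed to periodontal disease. Aim 1 would be answered with a less well-adjusted estimate than the trial's own data allow, and the two analyses that inherit the list would share the gap.

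**Working it through.** **1. Candidate variables set against the stated categories**

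| Variable | Where it appears | Fixed before the dental examination? | In the B-versus-C set? |
|---|---|---|---|
| Age, education, employment, asset-based socioeconomic score | Socio-demographic data | Yes | Yes |
| Smoking, diet, sleep, physical activity | Lifestyle | Yes | Yes |
| Study site | Study sites; Randomization and blinding | Yes | Not named |
| Pre-pregnancy BMI, maternal height | Antenatal records | Yes | No |
| Obstetric history | Surveys (own domain); Socio-demographic data (birth history) | Yes | Unclear |
| Gestational age at enrolment | Inclusion and exclusion criteria (threshold only) | Yes | No; not listed as a recorded item |
| Blood glucose | Antenatal records | Timing not stated | No |
| Complications, number of visits | Antenatal records | No, or not wholly | No, rightly |
| Pregnancy outcomes | A-versus-B list only | No | No, rightly |

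Site needs its own remark. Blocked randomisation at each site balances A and B within site, but nothing balances B and C.

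**2. Possible size**

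The protocol gives no figure for confounding to reproduce. It gives no confounder prevalences or risk ratios either, so every input here is an assumption. For one omitted binary factor with risk ratio RR for preterm birth and prevalence pB in B and pC in C, the observed B/C risk ratio is multiplied by

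[1 + pB(RR − 1)] / [1 + pC(RR − 1)].

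| RR | 15% vs 10% | 25% vs 15% | 40% vs 20% |
|---|---|---|---|
| 1.5 | 1.024 | 1.047 | 1.091 |
| 2 | 1.045 | 1.087 | 1.167 |
| 3 | 1.083 | 1.154 | 1.286 |

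Worked example for RR 3 at 40% vs 20%: (1 + 0.40 × 2) / (1 + 0.20 × 2) = 1.8 / 1.4 = 1.286. The range is about 2% to 29%. If the factor were commoner in C, the multiplier would be the reciprocal, from 1/1.024 = 0.98 down to 1/1.286 = 0.78. The prevalences should be read as the imbalance left after adjusting for socio-demographic characteristics and lifestyle.

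**3. How many terms the data can carry**

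Sample size calculation gives 128 analysable women per group and a preterm birth rate of 16.2%. Assuming that rate in both B and C, events = 2 × 128 × 0.162 = 41.5, about 41. Take a model with exposure, site, age, socioeconomic score, parity, previous preterm or low-birth-weight birth, BMI, height, gestational age at enrolment, smoking and diet, at one parameter each. It has 11 terms, so 41 / 11 = 3.7 events per term.

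**4. Sampling error on the same assumption**

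SE of the log risk ratio = √[2 × (1 − 0.162) / (128 × 0.162)] = √(1.676 / 20.736) = 0.284. The 95% interval spans a factor of exp(1.96 × 0.284) ≈ 1.75 either side of the estimate.

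**The case against.** A reader who sets the two covariate lists side by side might infer that they are the wrong way round: long where randomisation protects, short where it does not. The documents do not support that. The additional A-versus-B items include pregnancy outcomes, which arise after baseline, and an undefined group of pregnancy-related characteristics that could take in complications and visit counts. Restricting B versus C to baseline factors is right in principle, and the longer list is not a model to copy.

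Other points on that side also stand:

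- The stated set already covers age, socioeconomic score, smoking and diet, and arguably birth history.
- High-risk pregnancies, including those with diabetes or hypertension, are excluded, which removes some potential confounding.
- No passage shows that BMI, height or site is related to both periodontal disease and preterm birth in this population.
- Gestational age at enrolment and previous preterm birth are not listed as recorded items, so it cannot be said that everything desirable is already in hand.
- The planned bivariate comparison of B with C would reveal imbalance in measured baseline variables.
- Aim 1 is worded as an association; the protocol keeps causal language for A versus B.
- About 41 events cannot support a long covariate list.

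Itemising covariates within a category is properly left to a SAP, but that does not answer this point. BMI, height and site lie outside the named categories, so an analysis that followed the protocol as written would omit them. A bivariate table shows imbalance without correcting the estimate. Few events argue for a compact or penalised model, not for leaving out pre-exposure variables.

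**Conclusion.** The concern holds in limited form. The B-versus-C birth-outcome model omits study site, pre-pregnancy BMI and maternal height, and the protocol is inconsistent on whether obstetric history is included. Aim 1 is therefore open to confounding that is cheap to reduce.

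A reader might infer from the table of multipliers that the association will be inflated by up to 29%, or that several omitted factors would compound. Neither follows. The inputs are assumed, the bias could run either way, and multiplication across factors needs them to act roughly independently, which nothing in the protocol establishes. Even the top of the assumed range (1.29) is smaller than the sampling uncertainty (a factor of about 1.75 either side, if 16.2% applies in both groups at 128 each).

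The randomised primary comparison is untouched. This is a worthwhile low-cost improvement to a secondary aim.

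**What to change.** Amend the B-versus-C covariate statement so that it remains baseline-only and names, in addition to the present categories:

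- study site;
- pre-pregnancy BMI and maternal height;
- obstetric history (parity, and previous preterm or low-birth-weight birth where recorded), with Surveys and Socio-demographic data reconciled on where it belongs;
- gestational age at enrolment, which must be known to judge eligibility, if it is recorded.

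State that pregnancy complications, number of antenatal visits and pregnancy outcomes are not adjusted for in B versus C, and that the A-versus-B list is not carried over. Admit blood glucose only if it was measured by enrolment. Because events will be few, specify in advance either a compact set, a propensity score built from these variables, or a Firth-penalised logistic model. Say explicitly whether the periodontal-change and OHRQoL analyses in B and C use the revised set.

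The cost is analysis wording, a few more model terms and slightly wider intervals. Site, BMI and height need no new data collection; the remaining items are used only where recorded. Data collection is expected to run to September 2026, so the set can be fixed before it ends.

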##### Diagnosis of periodontal disease

BOP, PPD, and CAL will be measured at six points on each tooth and used to diagnose periodontal diseases, including gingivitis and periodontitis. Gingivitis is diagnosed when BOP is present at 10% or more of the total number of periodontal sites examined. Periodontitis will be diagnosed if either of the following criteria is met: (1) interdental CAL is observed at ≥ 2 non-adjacent teeth, or (2) a buccal or palatal/lingual site exhibits a CAL of ≥ 3 mm and PPD of ≥ 4 mm at ≥ 2 teeth [45, 46].

Participants diagnosed with periodontal disease will be randomized into either the intervention group A or control group B. Participants without periodontal disease will be allocated to control group C.

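### The B-versus-C analysis of change in periodontal status compares groups formed from the baseline value of that same status, so any diagnostic error produces a difference in change by regression to the mean

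*Protocol article*

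**What the plan says.** Group membership follows from the baseline dental checkup. Under Diagnosis of periodontal disease: "Participants diagnosed with periodontal disease will be randomized into either the intervention group A or control group B", and "Participants without periodontal disease will be allocated to control group C". Randomization and blinding says the same. The diagnosis rests partly on a cut-off: "Gingivitis is diagnosed when BOP is present at 10% or more of the total number of periodontal sites examined". Periodontitis has its own attachment-loss and pocket-depth limits.

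In Statistical analyses, the B-versus-C model for birth outcomes is set up "with baseline periodontal status (group B or C) as the exposure". The next sentence reads: "To assess change in periodontal status between baseline and endline in groups B and C, another multiple regression model will be used", with covariate adjustment like that of the birth-outcome model, that is, socio-demographic and lifestyle variables. It does not say whether change is measured as present/absent, as a grade or on a continuous scale.

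Three other statements bear on the point. The Discussion says that the endline dentists will not be those who did the baseline checkups. The Interventions section gives group B its periodontal treatment only after the endline checkup, so B is untreated between the two examinations. The general rule in Statistical analyses is "Mixed-effect regression models will be applied for outcomes assessed at both baseline and endline", whereas this analysis of a twice-measured outcome is assigned to multiple regression.

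**The concern.** The grouping variable is the baseline value of the variable whose change is analysed. Women enter B because one examination put them above a threshold, and C because it put them below. Some women close to the threshold are on the wrong side of it at that visit. A second examination with its own error, here by another dentist, moves some of B down and some of C up without any change in disease.

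Socio-demographic and lifestyle covariates do not act on this, because it comes from selection on the baseline measurement. On the present/absent scale, baseline status cannot be added as a covariate either, since it is identical to group. Using a mixed model, as the general rule would have it, does not help: its group-by-time term is the same difference in change.

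At stake is a significant result suggesting that untreated women with disease improved relative to healthy women, who deteriorated. It could be taken as evidence on the natural course in pregnancy, or on the education that all women receive. No stated aim needs this comparison. The Background gives B versus C the question of birth outcomes, and periodontal status appears there only as an effect of the intervention, which is A versus B.

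**Working it through.** The article gives no figure for this analysis, so there is none to reproduce. The check asks how large a B-versus-C difference in change arises when nobody's true disease changes.

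**Inputs from the article.** Prevalence: about 40% (global figure, Background) and 95.3% (Dhaka study, Background), used as the two ends. Evaluable women per group: 160 × 0.8 = 128 (Sample size calculation).

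**Assumed.** A normal latent score, the same distribution at both visits, baseline–endline correlation r = 0.7, 0.9 or 0.95.

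**Step 1: direction.** Code disease 1 and no disease 0. B starts at 1 and C at 0, so change is 0 or −1 in B and 0 or +1 in C.

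**Step 2: size.** For prevalence p, the cut-off is k = Φ⁻¹(1 − p). The share of all women who cross in one direction is d = (1 − p) − Φ₂(k, k; r). Then:

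- new disease in C = d/(1 − p)
- resolved disease in B = d/p
- spurious difference in change = the sum of the two
- z = difference / √[c(1 − c)/128 + b(1 − b)/128], with c and b the two proportions

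| p | r | d | C, new | B, resolved | Difference (points) | z |
|---|---|---|---|---|---|---|
| 40% | 0.70 | 0.1224 | 20.4% | 30.6% | 51.0 | 9.4 |
| 40% | 0.90 | 0.0695 | 11.6% | 17.4% | 28.9 | 6.6 |
| 40% | 0.95 | 0.0489 | 8.2% | 12.2% | 20.4 | 5.4 |
| 95.3% | 0.70 | 0.0289 | 61.4% | 3.0% | 64.4 | 14.1 |
| 95.3% | 0.90 | 0.0172 | 36.7% | 1.8% | 38.5 | 8.7 |
| 95.3% | 0.95 | 0.0123 | 26.1% | 1.3% | 27.4 | 6.8 |

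Hand check at p = 50%, r = 0.7: d = 1/4 − arcsin(0.7)/(2π) = 0.25 − 0.1234 = 0.1266, and the difference is 4d = 50.6 points. At r = 1, d = 0 and the difference is 0 at every prevalence.

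**Step 3: a second method.** Suppose independent errors at each visit with sensitivity and specificity both 0.95 (assumed), and p = 40%. Classed as diseased: 0.4 × 0.95 + 0.6 × 0.05 = 0.41. Truly diseased among these: 0.38/0.41 = 0.927. B resolves: 1 − (0.927 × 0.95 + 0.073 × 0.05) = 11.6%. Truly diseased in C: 0.02/0.59 = 0.034. C acquires disease: 0.034 × 0.95 + 0.966 × 0.05 = 8.1%. The difference is 19.6 points before rounding, z = 5.3. At p = 95.3% it is 56.7 points. With 0.90 in place of 0.95 the two figures are 36.9 and 75.8 points. With 1.00 both are 0.

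**Step 4: other scales.** If both visits have the same distribution, mean change over all women is zero, so p × (mean change in B) + (1 − p) × (mean change in C) = 0. Selection below the cut-off makes the C term positive, so the B term is negative. A simulation of the percentage of bleeding sites (assumed log-normal, median 15%, log-SD 0.9, cut-off 10%, reliability 0.9 down to 0.7) gave mean changes of −0.5 to −1.7 points in B and +1.1 to +3.6 in C. In the same simulation 42% to 45% of B women showed a rise.

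**The case against.** The strongest reply is that the challenged model is partly inferred. The sentence names no predictor and no outcome scale, and a condensed article may leave both to a fuller document. That stands as a limit. Still, the sentence before it uses group as exposure and this one announces another such model, so group as predictor is the natural reading. The selection problem does not depend on the scale.

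A reader might go further than the article allows in four ways.

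- That B can only improve, and that the sign is therefore fixed in advance. This holds only for present/absent status. The measurements are "used to diagnose periodontal diseases, including gingivitis and periodontitis", so on a graded scale a B woman can move from gingivitis to periodontitis, and on bleeding, pocket depth or attachment loss she can worsen freely. The bias keeps its direction, but the observed sign is not guaranteed.
- That a large difference appears whatever happens. Without true change it needs measurement error; with perfect diagnosis it is exactly zero. Some error is likely given the 10% threshold and the change of dentists, but the article does not quantify it.
- That 160 per group implies a prevalence of two thirds. Study population makes 160 a recruitment quota, which says nothing about prevalence.
- That the investigators will present the result as natural course or as an effect of education. The article does not say so. It reserves causal language for A versus B.

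It is also fair that this is one non-randomised secondary analysis. That limits the importance of the point without making the test interpretable.

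**Conclusion.** The point holds in this conditional form. Groups B and C are defined by the baseline value of the status whose change is to be modelled. Given any diagnostic error, regression to the mean pushes them in opposite directions, and the planned adjustment does not correct it.

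Under the assumed bivariate-normal model with no true change, the artefact is about 51 to 64 points at r = 0.7, 29 to 39 at r = 0.9 and 20 to 27 at r = 0.95. With 128 per group, z is at least 5.4 in each case, so significance at the planned 5% level is close to certain with no true change at all. These sizes rest on assumed reliability and on the two prevalence figures cited in the Background; at perfect reliability the artefact vanishes. The direction of the bias needs only some measurement error.

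The randomised A-versus-B comparison does not share this problem, because both arms were selected by the same baseline diagnosis. The primary outcome is not touched.

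**What to change.** Drop the between-group B-versus-C test of change in periodontal status. In its place report, separately and with confidence intervals:

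- the proportion of group C with new periodontal disease at endline;
- the proportion of group B whose disease persists at endline;
- the within-group change in percentage of bleeding sites.

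State beside each that regression to the mean contributes to it. Say that conclusions about change due to treatment come only from randomised A versus B.

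The cost is the loss of one secondary, non-randomised comparison that serves no stated aim. The replacement uses the planned baseline and endline checkups and needs no further data. Data collection is expected to run to September 2026 (Trial status), so the change can be made before analysis.

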### Study population

Pregnant women attending antenatal checkups will be recruited from the obstetrics and gynecology departments at both hospitals, targeting approximately 225 participants per site. Enrollment will continue until 160 participants are allocated to each study group. Trained healthcare professionals, such as doctors, dentists, nurses, midwives, and dental assistants, who have completed a training program led by the research team, will assess eligibility, explain the study procedures, obtain informed consent, and conduct the intervention.

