##### Oral health

Data on oral hygiene practices, especially tools, timing, and frequency of oral care, and knowledge of the epidemiology and prevention of periodontal disease will be collected. OHRQoL will be assessed via the Oral Health Impacts Profile (OHIP-14) [38, 39]. The profile consists of 14 questions in seven domains: functional limitation, physical pain, psychological discomfort, physical disability, psychological disability, social disability, and handicap. Responses are recorded, using a five-point Likert scale to record the responses: never = 1, hardly ever = 2, occasionally = 3, fairly often = 4, and very often = 5. The total score will be dichotomized into high versus low impact, using a median split.

The presence of periodontal disease symptoms will be assessed, using ten questions from a self-report check list developed by the Japanese Academy of Clinical Periodontology [40]. The questions include items related to bad breath, sticky mouth, bleeding during toothbrushing, swollen/drooping/bleeding gums, and problems with the teeth. The presence or absence of any symptoms will be included in further analysis.

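### The model relating baseline periodontal disease to OHRQoL leaves out group A's equally valid baseline records, which costs precision but not validity

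*Protocol article*

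**What the plan says.** The protocol article's Statistical analyses section restricts this analysis to two of the three groups: "To evaluate the association of baseline periodontal diseases and OHRQoL in groups B and C, mixed-effect regression models will be fitted". The model is longitudinal, "including baseline periodontal status (group B or C), time point (baseline or endline), and their interaction term", with adjustment for confounders.

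The order of events at baseline is set under Randomization and blinding: "All participants will first complete a face-to-face interview at the obstetrics and gynecology department following consent. They will then undergo a baseline dental checkup". OHRQoL belongs to that interview, as the Surveys section states: "Face-to-face interviews at baseline will collect data on socio-demographic characteristics, obstetric history, oral care behaviors, OHRQoL, and lifestyle". Only after the checkup are the diseased women divided: "Participants diagnosed with periodontal disease will be randomized to group A or B using blocked randomization". Women without disease form group C. Under Basic periodontal treatment and mouthwash use, group A's treatment starts after the baseline checkup.

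The planned group size is in Study population: "Enrollment will continue until 160 participants are allocated to each study group". The Oral health section gives the outcome scale for OHIP-14: "The total score will be dichotomized into high versus low impact, using a median split".

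**The concern.** Part of the question is whether women with periodontal disease at baseline report a worse oral-health-related quality of life than women without it. At that moment groups A and B do not yet exist as separate groups. All of these women are diseased and untreated, and none has been told a diagnosis or an allocation by the study. Group A's baseline OHIP-14 therefore measures the same thing in the same population as group B's, yet the plan uses only B's and gives no reason.

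The baseline contrast is also the part of the model least open to reporting bias. Participants are not blinded, so by endline women in B may know that they have untreated disease, and women in C that they are free of it. It would be better not to estimate the cleanest component from half of the available diseased women.

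**Working it through.** **Inputs**
- Planned group size: 160 in each of A, B and C (Study population; Sample size calculation).
- Order: interview with OHIP-14, then checkup and diagnosis, then allocation, then treatment of A (Randomization and blinding; Surveys; Basic periodontal treatment and mouthwash use).
- Outcome: OHIP-14 total split at the median (Oral health).
- The protocol gives no power, SD or expected difference for this analysis, so effect sizes below are assumptions.

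**The plan's own figure.** The 160 comes from the preterm birth calculation. A two-sided 5% test of 16.2% versus 4.7% with 80% power and a continuity correction gives 127 per group, against the stated 128. Then 128/0.80 = 160, and 3 × 160 = 480. The group size is reproduced, but it was not chosen with OHRQoL in mind.

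**Baseline contrast, planned size.** With equal variability in the groups, the variance of the difference is proportional to 1/n(diseased) + 1/n(C).
- B versus C: 1/160 + 1/160 = 0.0125.
- A+B versus C: 1/320 + 1/160 = 0.009375.
- Variance ratio: 0.009375/0.0125 = 0.75, a 25% reduction.
- Standard error ratio: √0.75 = 0.866, an interval 13.4% narrower.
- To get the same gain by recruitment, B and C would each need 1/0.75 = 1.33 times as many women.

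**Does this carry over to the median split?** A binary outcome weights each term by p(1−p) or its inverse. With an assumed 57% versus 43% high impact, p(1−p) = 0.2451 in both groups, so the ratio is again 0.75 for both the risk difference and the log odds ratio. Power for that assumed difference rises from 71% to 83%. With an assumed 50% versus 35%, the variance ratio is
- risk difference: (0.25/320 + 0.2275/160)/(0.25/160 + 0.2275/160) = 0.738;
- log odds ratio: (1/80 + 1/36.4)/(1/40 + 1/36.4) = 0.762.

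So about 25% is a fair summary on either scale.

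**If group C is smaller.** The Background cites a Dhaka study in which 95.3% of pregnant women had periodontal disease. If that held at the sites, enrolling 320 diseased women would bring 320/0.953 − 320 ≈ 16 women without disease, and 480 women in total would include 480 × 0.047 ≈ 23. With A and B held at 160 each, the standard error ratio is √[(1/320 + 1/n(C))/(1/160 + 1/n(C))]:

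| n(C) | Ratio | Interval narrower by |
|---|---|---|
| 160 | 0.866 | 13.4% |
| 80 | 0.913 | 8.7% |
| 23 | 0.968 | 3.2% |
| 16 | 0.977 | 2.3% |

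**Change component (status by time).** Suppose A enters at baseline only, with a baseline level shared with B, and let ρ be the within-woman correlation. On a linear scale with 160 per group, the variance of the difference in change is (7 + ρ)/8 of the planned one. That is 0.875 at ρ = 0, 0.9375 at ρ = 0.5 and 0.9625 at ρ = 0.7: a reduction of 12.5% down to about 4%. The range of ρ is assumed.

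**The case against.** The strongest reply is that nothing here is wrong. B is a random half of the diseased women, so B versus C estimates the same baseline difference as A+B versus C. The model is longitudinal, and A is treated straight after the baseline checkup, so two groups without the study treatment before endline make a coherent analysis set. The protocol sets no precision target for this association, which is ancillary: the stated aims link periodontal disease to birth outcomes, and link OHRQoL to the intervention.

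Most of that stands, and it rules out several stronger readings that a reader might infer:
- That B versus C is biased by omitting A. Randomization excludes this. Confounding between diseased and healthy women remains, but it is the same with or without A.
- That the plan estimates only a difference in change. With baseline as the reference time, the status term is the baseline contrast.
- That group A's OHRQoL data are lost to the trial. They are used in the A versus B mixed model.
- That A should also join the B versus C analysis of birth outcomes or the endline OHRQoL contrast. By then A has been treated, and its exclusion is right.
- That the fix cures the effect of knowing one's diagnosis at endline. It does not, because B versus C stays in use there.

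Two further objections shape the remedy. Detectable differences in SD units would describe a continuous score, whereas the plan analyses a median split. A sample median taken only within the analysed set could also move when A is added. Both call for care in the wording. Neither removes the gain in precision.

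**Conclusion.** The point holds as a minor gain in efficiency. Group A's baseline OHIP-14 records are valid for the diseased side and are left out of this model without a stated reason. Using them cuts the variance of the baseline contrast by about 25% and narrows its interval by about 13%.

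This size rests on 160 women in each group, complete baseline interviews and similar variability across groups. The number of women in C matters most: the interval is about 9% narrower with 80 of them and only 2-3% narrower with 16 to 23. The gain for the change component is smaller.

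The primary outcome, the randomized A versus B comparison and the validity of the planned B versus C estimate are unaffected.

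**What to change.** Amend the sentence on baseline periodontal disease and OHRQoL in Statistical analyses along these lines:
- Add group A's baseline records to the mixed model, with one baseline level common to A and B (justified by randomization) and a separate one for C.
- Report (A+B) versus C as the baseline association.
- Keep B versus C for the endline and change components, with A's endline records taking no part in them.
- Match the model to the scale analysed: a mixed logistic model if the median split is kept, with a single cut-point set once for all groups.

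The cost is a sentence or two of analysis wording. The records are already collected from every participant, so no new women, visits or measurements are needed. The report should state that the diseased sample is A+B at baseline and B alone at endline. Data collection is expected to run to September 2026 (Trial status), so the wording can be settled before the analysis.
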